**Primary outcome**						
	Health-related quality of life	St George Respiratory Questionnaire		✓		✓
**Secondary outcome**						
	Symptom burden	COPD^a^ assessment test		✓	Daily	✓
	Spirometry	Forced expiratory volume in one second		✓	Daily	✓
		Forced vital capacity		✓	Daily	✓
	Functional exercise capacity	1-minute sit-to-stand test		✓		✓
		6-minute walk test		✓		✓
	Compliance with COPD^a^ medication	Self-reported			Daily	
	Physical activity	Step count			Daily	
	Cough	Night-time cough count			Daily	
**Explanatory endpoints**						
	**System usability**					
		Questionnaires			Weekly	
		Focus group interviews				✓
	**Exacerbation and air quality**					
		Ex ante data		In case of event		
		Ex post data		In case of event		
		Volatile organic compounds			Continuously	

^a^COPD: chronic obstructive pulmonary disease.

### Statistical Analysis

Statistical analysis will be carried out after completing the data collection period, which will last around 18 months. We will not perform any interim analysis. We will use descriptive statistics to describe group characteristics and perform independent samples *t* tests to explore and identify potential differences at the primary endpoint (HRQOL) between the intervention and control group. We will compare the differences in the percentages of SGRQ (≥4 points) improvement between the control and intervention groups. The statistical analysis will be performed using the latest version of R (R Core Team 2019) for Windows. Missing data at the baseline and end of study visits will be handled through multiple imputation at the analysis stage. Factors prone to influence endpoints, such as gender, age, and the Global Initiative for Chronic Obstructive Lung Disease classification, will be assessed and accounted for in the analysis and interpretation of the data.

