## Methods

We will perform a monocentric, assessor-blind, two-arm (intervention/control) randomized controlled trial. The allocation ratio between the intervention and control group will be 2:1. Bias will be minimized through randomization, allocation concealment, assessor blinding, and statistical adjustment or subgrouping during the analysis. The study is expected to have an overall duration of 18 months (first patient in, last patient out). The length of study per patient will be 12 weeks. The recruitment period will last several months.

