#### Sample Size

Sample size calculations used a power of 80% and a two-sided significance level of 0.05. To increase usability reporting and account for possible dropouts, we decided to use a 2:1 (intervention:randomization) ratio and doubled the result of the sample size calculation. The sample size calculation yielded a total of 42 patients (28 intervention, 14 control). This sample size will result in an effect size of 0.9 to detect a clinically relevant between-group difference in the SGRQ.

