### Outcomes

#### Primary Outcome

As a primary outcome, we will measure the delta in HRQOL, which we will assess with the SGRQ [12] from baseline to week 12 (the end of the intervention). The SGRQ is a well-established self-administered questionnaire that is valid, reliable, and responsive for the population affected by COPD. Participants will not have access to their completed questionnaires and scoring to reduce potential bias.

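### The t test named for the SGRQ change takes no covariate and baseline SGRQ is not named for adjustment: valid, but less efficient than ANCOVA unless the two visits correlate at about 0.9 or more

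*Protocol article*

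**What the plan says.** Under Primary Outcome the article defines the endpoint as a change: "we will measure the delta in HRQOL, which we will assess with the SGRQ [12] from baseline to week 12". Table 1 shows the SGRQ at both the baseline and the end of study visit, so a baseline value is planned for every patient.

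Under Statistical Analysis the only test named for this endpoint is the independent samples t test: "tests to explore and identify potential differences at the primary endpoint (HRQOL) between the intervention and control group". A later sentence in the same section reads "Factors prone to influence endpoints, such as gender, age, and the Global Initiative for Chronic Obstructive Lung Disease classification, will be assessed and accounted for", and applies this to both analysis and interpretation. The three factors are given as examples, so the list is open. Baseline SGRQ is not one of them, no model is written down, and no adjusted estimate is made the primary one. The opening paragraph of Methods promises "statistical adjustment or subgrouping during the analysis" in general terms only. Multiple imputation is planned for values missing at the two visits.

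**The concern.** A t test on change fixes the coefficient of baseline at 1. ANCOVA estimates that coefficient and, when the two visits are less than perfectly correlated, gives a smaller standard error for the same treatment effect. The trial is small, with 28 intervention and 14 control patients, and its power statement leaves no slack. The unused information is already collected.

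Two things are at stake. The first is power. The second is how the result reads if the arms happen to start apart: part of that gap then remains in the change-score estimate, to be judged against the 4-unit minimal important difference given under Hypotheses.

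This concerns a stated choice and not a missing detail. The article names a test, and a later plan that made ANCOVA primary would depart from it.

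**Working it through.** **Inputs from the article.** Sample Size: "Sample size calculations used a power of 80% and a two-sided significance level of 0.05"; 28 intervention and 14 control patients; effect size 0.9. Hypotheses: minimal important difference of 4 SGRQ units.

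**Assumptions, not in the article.** The 0.9 is read as SDs of the change score. The SGRQ SD is equal at both visits. Rho runs from 0.5 to 0.9. The baseline SGRQ SD is 15 to 20 units.

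**1. The plan's own figure.** A two-sided t test with d = 0.9 and 80% power needs 20.4 per arm at 1:1, so 21 + 21 = 42. This matches the stated total. At the planned 28:14 split:
- SE factor: √(1/28 + 1/14) = 0.327.
- Noncentrality: 0.9 / 0.327 = 2.75.
- Power: 76.5% (noncentral t, 40 df), or 78.5% by the normal approximation.
- Effect detectable with 80% power: 0.94 (t) or 0.92 (normal), both of which round to the stated 0.9.

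**2. Gain from ANCOVA.** With visit SD σ, the per-patient variance is 2σ²(1 − rho) for the change score and σ²(1 − rho²) after adjustment for baseline. The ratio is (1 + rho)/2. Estimating the slope costs a factor 1 + 1/(42 − 4) = 39/38. The noncentrality is 2.75 divided by the square root of the resulting ratio, with 39 df.

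| rho | (1 + rho)/2 | × 39/38 | Noncentrality | ANCOVA power | Simulated |
|---|---|---|---|---|---|
| 0.5 | 0.75 | 0.770 | 3.13 | 86.3% | 86.5% |
| 0.6 | 0.80 | 0.821 | 3.03 | 84.1% | 84.2% |
| 0.7 | 0.85 | 0.872 | 2.94 | 81.9% | 82.0% |
| 0.8 | 0.90 | 0.924 | 2.86 | 79.7% | 79.8% |
| 0.9 | 0.95 | 0.975 | 2.78 | 77.5% | 77.8% |

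The simulations used 20,000 trials at rho 0.5, 0.7 and 0.9, and 8,000 at 0.6 and 0.8. The simulated t test had 76% to 77% power throughout. The gain is gone when (1 + rho)/2 × 39/38 = 1, that is, at rho of about 0.95.

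**3. Chance imbalance.** The baseline difference between arms has SE 0.327 × 15 = 4.9 to 0.327 × 20 = 6.5 units. A share (1 − rho) of any such difference, with opposite sign, stays in the change-score estimate. For a 1-SE imbalance the shift is:
- rho 0.5: 0.5 × 4.9 to 0.5 × 6.5, about 2.5 to 3.3 units.
- rho 0.7: 0.3 × 4.9 to 0.3 × 6.5, about 1.5 to 2.0 units.

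The chance that the shift exceeds 4 units is 10% to 22% at rho 0.5 and 0.7% to 4% at rho 0.7.

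**4. Steps 2 and 3 are one cost.** Algebraically 2(1 − rho) = (1 − rho²) + (1 − rho)². The first term on the right is the ANCOVA variance and the second is the imbalance left in the estimate. At rho 0.7 this is 0.60 = 0.51 + 0.09, and 0.51/0.60 = 0.85, the ratio in the table. The t test's standard error already includes the imbalance.

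**The case against.** The t test on change is a legitimate analysis. Under randomisation it has correct type I error and an unbiased estimate, and it fits the endpoint as defined. This stands in full: the point is one of efficiency.

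The adjustment list is open, and a separate analysis plan could add baseline SGRQ. This stands in part. The wording does not exclude baseline SGRQ, and the article need not list every covariate. But an open list of factors does not turn the named test into a baseline-adjusted one.

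Every magnitude rests on a correlation and an SD that the article does not give. This also stands, and it is why ranges are shown.

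A reader might infer four stronger things that the article does not support:
- **That baseline SGRQ is ignored.** It is not: the change score subtracts it. What is absent is baseline as a covariate.
- **That the estimate is biased.** The shift is conditional error within one trial and averages out over randomisations.
- **That imbalance often exceeds the 4-unit threshold.** With the assumed SDs, the baseline gap itself exceeds 4 units in 42% to 54% of trials. Only the share (1 − rho) reaches the estimate, so the relevant frequencies are those in step 3 of the working.
- **That ANCOVA always restores the planned 80%.** It falls marginally short at rho 0.8 (79.7%) and stays clearly below at 0.9.

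**Conclusion.** The point holds as an avoidable loss of efficiency. It is not an invalid analysis. The named primary test has no covariate, and baseline SGRQ, though collected, is not named for adjustment.

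At 28:14 and 0.9 SD of change, adding it would raise power by about 10 percentage points at rho 0.5, 5 at rho 0.7, 3 at rho 0.8 and 1 at rho 0.9. The gain is material in the lower part of that range and negligible from about 0.9. The imbalance shift is the same imprecision seen within a single trial and must not be counted as a further harm.

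That baseline SGRQ is not named can be read directly from the article. The size of the loss depends on the assumed rho, the assumed SD and equal variance at the two visits. The change is worth making because it costs almost nothing; the trial would not be unsound without it.

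**What to change.** Before outcome data are seen, state one primary analysis: ANCOVA of week-12 SGRQ (or, equivalently for the treatment effect, SGRQ change) on arm and baseline SGRQ, fitted within the planned multiple imputation. Keep the unadjusted independent samples t test on change as a sensitivity analysis. If age, sex and GOLD class are to be adjusted for, put them in one fixed sensitivity model stated in advance.

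The cost is a few sentences and one degree of freedom. No new data or visits are needed. The article plans no interim analysis and analyses only after data collection, which leaves room to fix this wording before any outcome is examined.

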### Ethics and Dissemination

The study has received approval by the Ethics Committee of the Canton of Zurich and was registered in ClinicalTrials.gov (identifier: NCT04373070).

After the statistical analysis of this study, overall and subordinate findings will be submitted for publication in peer-reviewed journals. Dissemination of the results will be independent of negative or positive findings. The principles of the American Psychological Association guidelines for authorship eligibility will be followed.

## Results

The development of the CAir Desk and virtual coach is completed. Recruitment to the trial started in September 2020. We expect to start data collection by December 2020. This is 5 months behind schedule, which is due to the outbreak of COVID-19 that heavily impairs patients with COPD. Data collection is expected to last for approximately 18 months (first patient in, last patient out), as we follow a multiwave approach. The length of study per patient will be 12 weeks. The limited amount of available CAir Desks prevents us from executing a larger number of interventions simultaneously. We expect to complete data collection by mid-2022 and plan the dissemination of results subsequently.

## Discussion

### Study Contributions

To our knowledge, this is the first study investigating a combination of telemonitoring and hybrid virtual coaching in patients with COPD. We will investigate the effectiveness, efficacy, and usability of the proposed intervention and thus provide evidence to further develop app-based and chatbot-based disease monitoring and interventions in COPD. The study may also be extended to other respiratory diseases (eg, cystic fibrosis and COVID-19) and with an adapted technical setup to other chronic diseases requiring long-term treatment (eg, diabetes mellitus type 2 and chronic kidney disease).

### Strengths and Limitations

Randomized controlled trials are considered the “gold standard for evaluating efficacy in clinical research and constitute evidence for medical treatment” [25]. By adopting such a trial and ensuring internal as well as external validity, we maximize the robustness of our study. To make sure that the CAir Desk will function well with the study population, we extensively pretested the device in patients with COPD. The technology we used as part of the CAir Desk is well established and not likely to malfunction in daily use. A possible limitation is that the intervention is rather technology-heavy and the study population includes persons aged 45 years and older. Even though we pretested the system usability extensively in patients with COPD from the same population, some participants might feel overwhelmed and therefore discontinue the study. In addition, patients may feel overloaded by the daily measurements and questionnaires to be answered, which could also lead to dropouts. Another possible limitation is the limited size of the sample, given the heterogeneity in the population affected by COPD.

## Abbreviations

COPD: chronic obstructive pulmonary disease
HRQOL: health-related quality-of-life
SGRQ: St. George Respiratory Questionnaire
